**TBD**

3. Background

Preterm delivery rates in developed countries, including Israel, vary between 5-11%^[[1]](#endnote-1),^^[[2]](#endnote-2)^. Nosocomial infections (NIs) are a major health problem among premature infants, and are associated with increased morbidity, mortality, length of hospital stay, and costs^[[3]](#endnote-3),^^[[4]](#endnote-4)^. Overall infection rates range from 8.9 to 62 infections per 1,000 patient days^[[5]](#endnote-5)^’^[[6]](#endnote-6)^. Over the last 25 years, the improvement in survival of premature infants was paralleled by an increased rate of nosocomial infections (NI), especially among very low birth weight (VLBW) infants, who develop NI in 21-43% of cases^3^. This incidence is inversely related to gestational age and birth weight and directly correlated with severity of illness, length of stay, ventilation, central catheters, parenteral nutrition days, and broad spectrum antibiotics.

The emergence of multidrug- resistant organisms (MDRO) in acute-care settings, including the neonatal intensive care unit (NICU) , complicates the antimicrobial therapy and highlights the urgent need to limit the spread of such organisms and reduce the rate of NIs. Resistant organisms such as methicillin-resistant *Staphylococcus aureus* (MRSA), extended-spectrum beta-lactamase producing enterobacteriacae (ESBL) and carbapenem resistant *Acinetobacter baumanii* (CRAB) have caused outbreaks with associated morbidity and mortality in NICUs around the world ^[[7]](#endnote-7)^’^[[8]](#endnote-8)^’^[[9]](#endnote-9)^ . A stay in the NICU for > 1 week is a prominent predictor of colonization with resistant organisms^[[10]](#endnote-10)^. Strategies that have been utilized to limit the spread of MDRO within ICU’s have included stricter attention to barrier precautions following identification of patients colonized with these organisms, as well as improved handwashing. One prominent strategy that has emerged as recommended by recent SHEA guidelines ^[[11]](#endnote-11)^suggests that hospitals should adopt more aggressive active surveillance culturing to identify patients colonized with MDRO at the time of admission and periodically during their hospital stay. It is advocated, that under this “search and isolate” strategy, once reservoirs of resistant organisms within the hospital are identified, nosocomial transmission can be effectively eliminated through the use of strict barrier precautions and hand hygiene for these previously unidentified patients. However, this “search and isolate” strategy has multiple flaws. First, it is costly and requires high level of compliance with contact precautions and hand hygiene among healthcare personnel. Second, this strategy does little to eradicate colonization.

*As long as patients remain colonized, the opportunity for transmission exists. Therefore, a strategy that may address skin carriage of pathogens has the potential to reduce horizontal transfer to other patients as well as reduce the colonized patient’s risk to develop infection.*

The guidelines for preventing intravascular catheter-related infections published by the Centers for Disease Control and Prevention (CDC) recommend daily skin cleansing of ICU patients with 2% chlorhexidine to reduce catheter-related bloodstream infections (BSI)^[[12]](#endnote-12)^, but could not recommend its use in infants < 2 months of age due to lack of safety and efficacy data.

Chlorhexidine gluconate (CHG) is a broad spectrum antiseptic agent that maintains residual activity on patient’s skin. As a result, it may reduce efficiently the bacterial burden on the skin and prevent secondary environmental contamination ^[[13]](#endnote-13)^.It is now recognized that chlorhexidine is superior to other agents in site preparation for invasive procedures. The use of chlorhexidine reduces residual skin organisms as well as inhibits their rebound growth and has been demonstrated to reduce central-line associated bloodstream infection (CLABSI) in comparison to other skin disinfectant products such as povidone-iodine^[[14]](#endnote-14)^.

The same properties that make chlorhexidine an effective agent in the prevention of CLABSI have been utilized in selective settings to reduce the incidence of MRSA within the ICU.

Chlorhexidene has been used successfully to eradicate MRSA skin colonization ^[[15]](#endnote-15)^’^[[16]](#endnote-16)^.

The reduction in skin colonization with MRSA is thought to lead to reduced risk for horizontal transmission of MRSA within the ICU environment.

The use of chlorhexidine has been used successfully in the control of a number of MRSA

outbreaks within the NICU setting ^[[17]](#endnote-17)^’^[[18]](#endnote-18)^’^[[19]](#endnote-19)^. Although the selective use of chlorhexidine for catheter site preparation and in the selective treatment of MRSA colonized patients

during outbreaks has been investigated , there is little study of the potential utility of

more wide scale use of chlorhexidine in daily bathing routines , especially in the NICU. With

daily chlorhexidine bathing , there is the potential to reduce a number of NI, including CLABSI by reducing bacterial burdens on the skin. Reductions in resident bacteria on the skin could lead to reduced horizontal transmission of multiresistant bacterial pathogens and better outcomes following invasive procedures .

*Daily bathing to produce a state of skin asepsis is an attractive theorectical means to reduce nosocomial infections because it represents a simple intervention that could be applied universally with relatively little effort.*

A recent multicenter study examined the use of chlorhexidine-impregnated washcloths among adult patients at nine intensive care and bone marrow transplantation units. The chlorhexidine group had 23% lower rate of MDRO acquisition and a 28% lower rate of BSI compared with the control group ^13^. A systematic review of 15 studies, 9 of which were randomized controlled trials, provided support for the usefulness of CHG in a variety of healthcare settings including intensive care units, internal and surgical hospital wards ^[[20]](#endnote-20)^ .

Studies that examined the use of CHG in neonates were conducted mainly in developing countries and evaluated single whole body cleansing of the newborn immediately after birth, with or without maternal vaginal cleansing. CHG concentrations varied between 0.25% and 1%, and its use was associated with a reduction in neonatal mortality in high-mortality settings, but did not show benefit in low neonatal mortality settings^[[21]](#endnote-21)^’^[[22]](#endnote-22)^’^[[23]](#endnote-23)^’^[[24]](#endnote-24)^’^[[25]](#endnote-25)^’^[[26]](#endnote-26)^ . A large multicenter study in 10 pediatric intensive care units (PICUs) in the USA found that the incidence of bacteremia was 36% lower among patients receiving daily CHG bathing (3.28 per 1,000 days, 95%CI 2.27–4.58)) compared with patients receiving standard bathing practices (4.93 per 1,000 days, 95%CI 3.91–6.15 ). There were no serious study related adverse events^[[27]](#endnote-27)^.

Despite the fact that CHG was not approved by the US Food and Drug Administration for use in infants <2 months of age, it was used in large well-designed clinical trials on tens of thousands of neonates without reported serious adverse events^[[28]](#endnote-28)^’^[[29]](#endnote-29)^. Moreover, a recent survey in US NICUs found that the majority were using CHG, mainly for central venous catheter (CVC) site preparation and CVC maintenance ^[[30]](#endnote-30)^.

A recent study examined the effect of 2%CHG bathing on prevention of central-line associated bloodstream infection (CLABSI) in the NICU. Eligible infants were those with CVC weighing >1000 grams or those weighing <1000 grams after day 28 of life. Using a quasi-experimental study design the authors compared the rate of infection among infants before and after the intervention and demonstrated a decrease from 6 to 1.92/1000 CVC-days. No adverse events were reported^[[31]](#endnote-31)^.

Recently, the Israeli Ministry of health published guidelines that endorsed the use of 2%CHG solutions for the insertion of umbilical catheters. Shortly after, a national program for the reduction of NIs in Israeli NICUs was launched and encouraged the use of bundled practices including the use of 2%CHG for insertion and maintenance of central and peripheral catheters. The rate of CLABSI and BSI remains high in the NICU despite compliance with consensus guidelines and infection control measures. Lack of evidence from randomized trials prompt us to examine the usefulness of bathing with CHG to reduce the risk of CLABSI and BSI among infants in the NICU.

**4. Expected significance**

National data from the USA indicate that almost a quarter of very low birth weight infants will have one or more episodes of sepsis. Compared with infants without sepsis, infants with sepsis had a significantly longer hospital stay (79 vs.60 days), had a 2-fold increase in the number of days on mechanical ventilation, and had a significantly higher mortality rate (18% vs 7%)3. Another American study estimated that, on average, the cost of NICU care was $16,800 greater per infant who experienced NICU-associated BSI^[[32]](#endnote-32)^. Approximately 7% of infants, or >12,000 infants, are born prematurely in Israel every year^[[33]](#endnote-33)^. Extrapolating the American data to the Israeli NICU translates into a major health problem. The Ministry of Health and the Israel Neonatal Society have recently launched a national program aimed at minimizing the rate of NI in the Israeli NICUs^33^. In our NICU we have adopted this program and have increased staff education, active monitoring of compliance with guidelines, as well as adoption of the “search and isolate” policy, with twice a week screening of patients for colonization with MDRO.

Despite these measures, BSI rates remain high in our NICU, which prompt us to search for additional interventions such as CHG baths. The goal of the currently proposed study is to determine if universal use of a chlorhexidine based bathing system for patients in the NICU will decrease skin bacterial burden and lead to decreased horizontal transmission of MDRO.

Additionally, we hypothesize that reduced skin colonization with opportunistic bacterial

pathogens will result in a reduction in the rate of CLABSI, BSI and clinical sepsis in comparison to regular bathing procedures.

**5. Research design and Methods**

**5.1 Hypothesis:**

A change in the regular bathing procedures in the NICU to utilize products containing chlorhexidine will result in a reduction in the number of colonizing bacteria on the

skin of patients. Reduced colonization of the skin (skin asepsis) will lower the incidence of

nosocomial transmission of bacteria in the ward and decrease incident cases of new

bacteremias .

**5.2 Design**

This is a prospective, controlled; crossover study of daily bathing with no-rinse, 2% CHG impregnated washcloths versus bathing with water/soap or water according to gestational age and weight (e.g. standard bathing).

The primary study outcome is CLABSI/ BSI and clinical (culture-negative) sepsis.

Secondary study outcomes are rate and time to colonization with pathogenic bacteria.

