**1. Study Synopsis**

| Protocol Title | Evaluation of the Effectiveness of Chlorhexidine Bathing in Reducing Nosocomial Infections in the Neonatal Intensive Care Unit |
| --- | --- |
| Protocol Number |  |
| Sponsor |  |
| Primary objective | To determine if daily bathing with chlorhexidine impregnated  washcloths will reduce the incidence of bloodstream infections within the neonatal intensive care unit (NICU) . |
| Study design | This is a prospective, controlled; crossover study of daily bathing with no-rinse, 2% CHG impregnated washcloths versus bathing with water/soap or water according to gestational age and weight (e.g. standard bathing). The trial will take place in the NICU.  **In the preliminary phase of the study we will establish the safety of chlorhexidine bathing using Clinell ® Chlorhexidine wash cloths on three groups of patients: term infants admitted to the NICU; late preterm infants (34-37 weeks); preterm infants 30-34 weeks of gestation. Interim analysis for adverse events will be performed after each group of patients.**  **In the subsequent phases of the study,** all infants admitted to the NICU and enrolled in the study will be bathed three times a week with Clinell ® Chlorhexidine wash cloths during the initial 6-months study period (intervention), followed by standard bathing during the second 6-months period, then again intervention period for 6 months and standard bathing for 6-months. Total study period- 2 years.  Data collection will include all bloodstream infections as well as surveillance cultures |
| Number of subjects | Approximately 800 patients in both arms  **Up to 60 patients (at least 200 patient days) in the preliminary study** |
| Study population | Infants **>=10** days ,weighing **>=1500** grams admitted to the NICU |
| Duration of participation | Duration of NICU stay OR for the duration of invasive hardware (e.g intravacular catheters, nasogastric tubes etc. ) |
| Treatment | Bathing three times a week with either:  a.2% chlorhexidine gluconate cloth  b. water/mild soap +water |
| Assessment of efficacy | The primary efficacy endpoint will be the reduction in bloodstream infections incidence during those study periods where the 2% Chlorhexidine Gluconate Cloth will be utilized.  Additional study endpoints include overall incidence of colonization with multi-drug resistant organisms (MDRO) and time to colonization |

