**5.6 Outcome measures**

A. Number of BSI/CLABSI/clinical sepsis events per 1000 patient days during the intervention periods compared with the control periods.

B. Number of new patients colonized with MRSA, VRE, CRAB or ESBL per total number of patients, monthly range and variance.

C. Number of new patients colonized with MRSA, VRE, CRAB or ESBL per 1000 eligible patient days [ Total patient days – total patient days for patients identified with MDRO]

D. Time to colonization with MDRO during the intervention periods compared with the control periods.

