**5.7 Data collection**

Each patient admitted to the NICU during the study periods and meeting the inclusion criteria, will be recorded and assigned a specific study number. The dates of admission and dates of discharge will be recorded and used to calculate length of stay and to determine the

incidence of nosocomial infections based on microbiological data. Clinical and laboratory data, including the use of invasive device (intravascular devices, mechanical ventilation, feeding tubes) will be collected on standardized forms. The data will be coded under a password protected database and linked only to study patient identifier.

Infections and MDRO acquisitions will be monitored during the study period. Events occurring within 2 days after the transition will be assigned to the previous bathing period.

For infection surveillance, daily review of cultures and new orders for antibiotic therapy will be performed for all study participants. Infectious events will be evaluated by an independent investigator blinded to the intervention period.

Active surveillance testing for MDRO will be performed once every two weeks during the study period. Swabs from the nasopharynx (for MRSA)] and from the rectal area (for ESBL producing organisms, VRE and CRAB) will be obtained by unit staff and processed in the microbiology laboratory of Shaare-Zedek Medical Center.

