**5.9 Statistical analyses**

Changes in the rates of BSI and clinical sepsis will be compared between the intervention and the control period. Continuous variables will be examined with the use of two-sample t-tests and linear regression modeling, and categorical variables will be examined by means of Fisher’s exact test. Cox proportional-hazards regression model will be used to compare the time from admission until the first primary bloodstream infection , clinical sepsis or acquisition of MDRO between the control and intervention periods.

**Sample size calculation:** based on our ongoing surveillance, there are 2-3 BSI events per 1000 patients –days in our NICU. In order to detect a 50% reduction in BSI rates , we will need 37,096 patient days (18,548 in each group) in order to have 80% power to reject the null hypothesis, with 0.05 level of significance. Currently, our average annual census is 45,000 patient days. therefore, a 2-year study will have >80% power to reject the null hypothesis (the BSI rates in the control period equal the rates in the intervention period).

**For the preliminary study, we used the data in Milstone et al. ^18^ who reported no serious adverse skin reactions and an incidence of 1.2 minor skin reactions per 1000 patient days. A sample of 500 patient days will enable us to detect a ten-fold higher rate of minor skin reactions. Therefore at least 200 patient days in each group of the preliminary study (>600 patient days), would suffice.**

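### The primary endpoint is bloodstream infection alone in the synopsis but includes culture-negative sepsis in section 5.2, and only bloodstream infection has a sample size calculation

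*Protocol*

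**What the plan says.** - **Protocol, 1. Study Synopsis.** The primary objective concerns BSI incidence. Under assessment of efficacy: "The primary efficacy endpoint will be the reduction in bloodstream infections incidence". Clinical sepsis is not mentioned.
- **Protocol, 5.1 Hypothesis.** Among infections, only new bacteremias are named.
- **Protocol, 5.2 Design.** "The primary study outcome is CLABSI/ BSI and clinical (culture-negative) sepsis". The secondary outcomes listed there concern colonization only.
- **Protocol, 5.6 Outcome measures, item A.** "Number of BSI/CLABSI/clinical sepsis events per 1000 patient days", compared between intervention and control periods. The item is not labelled primary.
- **Protocol, 5.9 Statistical analyses.** "Changes in the rates of BSI and clinical sepsis will be compared between the intervention and the control period". The Cox model in the same section also takes in clinical sepsis. The sample size paragraph uses BSI only: 2-3 events per 1000 patient-days, a 50% reduction, 80% power, a 0.05 level, 18,548 patient-days per group.
- **Protocol, 5.7 Data collection.** "daily review of cultures and new orders for antibiotic therapy will be performed for all study participants". Events are then assessed by an independent investigator blinded to the period.

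**The concern.** The synopsis and section 5.2 each fix the primary outcome, and they fix it differently. If BSI and the wider outcome point in different directions, the protocol supports reporting either as the primary result. A single fixed primary outcome matters particularly here, because the whole unit uses one bathing method at a time in 6-month blocks and the staff know which.

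Three consequences follow.

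1. The planned size was derived for one of the two definitions only.
2. The wording in 5.2 does not say whether the outcome is one combined event count or several outcomes, or how a CLABSI, which is itself a BSI, enters the count.
3. The definitions differ in how open they are to knowledge of the bathing period. A culture-negative episode cannot be found through a positive culture. Of the two surveillance routes in 5.7, that leaves new antibiotic orders, which are written by clinicians who know the period. The blinded assessor protects the classification of episodes, but not the decision to work up or treat an infant.

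**Working it through.** **1. The definitions side by side**

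| Place in protocol | BSI | Culture-negative sepsis | Called primary? |
|---|---|---|---|
| Synopsis, objective and endpoint | yes | no | yes |
| 5.1 Hypothesis | yes (bacteremias) | no | – |
| 5.2 Design | yes, with CLABSI | yes | yes |
| 5.6 A | yes, with CLABSI | yes | no |
| 5.9 comparison | yes | yes | no |
| 5.9 sample size | yes | no | – |

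The direct contradiction is between the synopsis and 5.2. Sections 5.6 A and 5.9 show that the split runs through the rest of the document.

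**2. The plan's own figure**

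For two Poisson rates, patient-days per group = (z_α + z_β)² (r1 + r2) / (r1 − r2)².

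- With r1 = 0.002, r2 = 0.001, one-sided 0.05 and 80% power: (1.645 + 0.842)² = 6.1826, and 6.1826 × 0.003 / 0.001² = 18,548. This matches exactly.
- Two-sided at 2.5 per 1000: 7.849 × 0.00375 / 0.00125² = 18,838, within 3% of the stated figure.
- Two-sided at 2 per 1000: 23,547, which does not match.

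The protocol does not state sidedness. On either matching route, the only inputs are a BSI rate and its halving. No clinical sepsis rate or effect enters.

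**3. Power of BSI alone at 18,548 days per group, two-sided 0.05**

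Power = Φ(z − 1.96), with z = (r1 − r2) / √((r1 + r2)/n). At 2.5 versus 1.25 per 1000, z = 0.00125 / √(0.00375/18,548) = 2.78, so power is 79%. At control rates of 2 and 3 per 1000 it is 70% and 86%.

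**4. Power of BSI plus culture-negative sepsis on the same basis**

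The protocol gives neither the frequency of culture-negative sepsis nor the expected effect on it, so both are assumptions here. BSI is 2.5 per 1000 and is halved in every cell. The total control rate is set at 1.5, 2 or 3 times the BSI rate.

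| Total control rate per 1000 | No effect on culture-negative sepsis | 25% reduction | 50% reduction |
|---|---|---|---|
| 3.75 | 58% | 79% | 93% |
| 5.0 | 44% | 81% | 98% |
| 7.5 | 31% | 86% | >99% |

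Two cells worked out:

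- Lowest: 7.5 versus 6.25 per 1000, z = 0.00125 / √(0.01375/18,548) = 1.45, power 31%.
- Highest: 7.5 versus 3.75 per 1000, z = 0.00375 / √(0.01125/18,548) = 4.81, power above 99%.

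**5. Effect of a larger size**

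Section 5.9 gives a unit census of 45,000 patient-days a year. If all of these counted, two years would give 45,000 per arm, and the no-effect column would become 92%, 81% and 62%.

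**The case against.** **Is the wider outcome underpowered?** A reader might infer this, because it has no calculation. The documents do not support it. A wider outcome has more events, and section 4 (Expected significance) hypothesises a reduction in clinical sepsis as well as in CLABSI and BSI. If culture-negative sepsis were also halved, power would rise to 93% or more. With a 25% reduction it would be about the same as for BSI alone or somewhat higher. The low figures need an assumption of no effect, which runs against the protocol's own hypothesis, and they use the minimum size rather than the larger census. This objection stands: the direction of the change in power is unknown.

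**Are there several primary tests, or double counting?** A reader might infer that BSI, CLABSI and clinical sepsis are each tested at 0.05, or that CLABSI is added to BSI. Neither is stated. The slash reads naturally as one category, and 5.9 does not list CLABSI separately. Treating three tests as independent would also be wrong, since CLABSI is nested in BSI. What remains is that the wording in 5.2 should say how events are counted.

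**Is detection bias specific to sepsis?** No. Staff who know the period also decide when to draw blood cultures, so BSI shares the problem. Culture-positive BSI still needs laboratory confirmation, so the difference is one of degree. Blinded assessment helps, but only for episodes already worked up or treated.

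**Is clinical sepsis a legitimate outcome?** Yes. The fault lies in its unresolved primary status, not in measuring it.

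**Conclusion.** The contradiction between the synopsis and section 5.2 is plain, and nothing in the protocol resolves it. It should be settled before any data are compared, because it leaves open which result decides the trial.

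Only BSI has a power calculation. The wider outcome's power is undetermined. The range of about 31% to above 99%, against 79% for BSI alone, rests on a BSI rate of 2.5 per 1000 that is halved, two-sided 0.05, 18,548 patient-days per group, independent Poisson events, and assumed frequencies of and effects on culture-negative sepsis that the protocol does not give. The range shows that the calculation is missing. It does not show that the trial is too small for the wider outcome.

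The greater dependence of culture-negative sepsis on unblinded treatment decisions is a secondary reason to prefer BSI as primary.

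**What to change.** State one primary outcome in the same words in the synopsis, 5.2, 5.6 A and 5.9.

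- **Choice that fits the existing objective, hypothesis and sample size:** culture-positive BSI per 1000 patient-days of eligible infants, each event counted once, with CLABSI as a subset. List CLABSI and culture-negative sepsis as secondary outcomes in 5.2. In 5.9, mark which comparison and which Cox endpoint is primary. Section 5.6 C uses eligible patient-days for an MDRO-free denominator, so define the term separately for the primary outcome.
- **If the sponsor prefers the composite:** define it as a single event count, say how a CLABSI and a repeat episode enter it, and redo the sample size with the composite's own rate and expected effect. Amend the synopsis to match.

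Under either choice, reporting blood cultures drawn per 1000 patient-days by period would show whether sampling differed between periods.

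Cost: wording in four places for the first choice, plus a new calculation and a clinical sepsis rate for the second. Section 5.7 already provides for review of cultures and recording of device use. It does not specify counts of catheter-days or of cultures drawn, so these may need adding to the forms if CLABSI is to be reported per catheter-day or sampling is to be checked.

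### The protocol defines its primary endpoint in two conflicting ways, and the stated 80% power belongs to only one of them

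*Protocol*

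**What the plan says.** Two places in the protocol label something as primary, and they differ.

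- **Synopsis.** The objective is to learn whether the "washcloths will reduce the incidence of bloodstream infections within the neonatal intensive care unit (NICU"), and the efficacy row states: "The primary efficacy endpoint will be the reduction in bloodstream infections incidence". Clinical sepsis does not appear there. The additional endpoints listed are colonization with resistant organisms and time to colonization.
- **Section 5.2.** "The primary study outcome is CLABSI/ BSI and clinical (culture-negative) sepsis".

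The other sections do not settle the matter.

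- **Section 4** expects CLABSI, BSI and clinical sepsis all to fall. **Section 5.1** speaks only of bacteremias.
- **Section 5.6 A** counts the events together: "Number of BSI/CLABSI/clinical sepsis events per 1000 patient days during the intervention periods compared with the control periods". It is listed first but is not labelled primary.
- **Section 5.9** opens with "Changes in the rates of BSI and clinical sepsis will be compared between the intervention and the control period" and does not say whether the two are combined or compared separately. Its sample size paragraph is about BSI only: a background of 2 to 3 BSI per 1000 patient days, then "In order to detect a 50% reduction in BSI rates", 18,548 patient days per group, 80% power at the 0.05 level, and a null hypothesis of equal BSI rates.

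The protocol gives no rate or expected effect for clinical sepsis and does not say which definition prevails.

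**The concern.** Section 5.2 itself describes clinical sepsis as culture-negative. It therefore adds events that are not BSI; it does not reword the same endpoint. Three things are at stake.

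- **Conflicting answers.** If chlorhexidine bathing prevents BSI but has little effect on culture-negative sepsis, the added events dilute a real effect. One definition could then succeed while the other fails.
- **Power.** A power statement belongs to the endpoint whose rate and effect produced it. Here that endpoint is BSI.
- **Error rate.** If the conflict is still open when results are known, either definition could be called primary, and the 5% level would no longer hold.

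Clinical sepsis is also the component more exposed to knowledge of the bathing period. Section 5.7 finds events through cultures and new antibiotic orders, and ward staff can see which bathing product is in use. A culture-negative event has no positive culture to anchor it.

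**Working it through.** **Inputs from section 5.9:** BSI 2 to 3 per 1000 patient days (midpoint 2.5 used here), 50% reduction, 80% power, level 0.05, 18,548 patient days per group. Sidedness is not stated; two-sided is taken.

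**Assumed, because the protocol gives no figure:** clinical sepsis at 1, 2 or 3 per 1000 patient days, and either unaffected, reduced by 25% or halved.

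**Step 1. Reproduce the stated size.** Treat patient days as units, with p1 = 0.0025, p2 = 0.00125 and mean p = 0.001875:

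n per group = [1.960 × √(2p(1−p)) + 0.842 × √(p1(1−p1) + p2(1−p2))]² / (p1 − p2)²

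= [0.11991 + 0.05148]² / 0.00125² = 18,801

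This is within 1.4% of the stated 18,548, at which power is 79.5%. A one-sided test at 2.0 against 1.0 per 1000 also fits (18,519). Both routes use a BSI rate only, so the trial was sized for BSI.

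**Step 2. Power for BSI plus clinical sepsis at the same 18,548 days per group.** With sepsis rate s per 1000 and sepsis rate ratio r, the composite rates are c = (2.5 + s)/1000 in control and t = (1.25 + r·s)/1000 under intervention. With m = (c + t)/2:

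power = Φ{ [(c − t)√18,548 − 1.960 × √(2m(1−m))] / √(c(1−c) + t(1−t)) }

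| Sepsis per 1000 | Sepsis effect | Composite per 1000, control to intervention | Rate ratio | Power |
|---|---|---|---|---|
| 1 | none | 3.5 to 2.25 | 0.64 | 61% |
| 2 | none | 4.5 to 3.25 | 0.72 | 49% |
| 3 | none | 5.5 to 4.25 | 0.77 | 41% |
| 1 | −25% | 3.5 to 2.0 | 0.57 | 79% |
| 2 | −25% | 4.5 to 2.75 | 0.61 | 80% |
| 3 | −25% | 5.5 to 3.5 | 0.64 | 82% |
| 1 | −50% | 3.5 to 1.75 | 0.50 | 91% |
| 2 | −50% | 4.5 to 2.25 | 0.50 | 96% |
| 3 | −50% | 5.5 to 2.75 | 0.50 | 99% |

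For comparison, BSI alone has 79%.

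**Step 3. False-positive chance if the primary were chosen after seeing the data.** With no effect on either component, the BSI and composite test statistics are approximately bivariate normal with correlation √(BSI share of composite events). The chance that at least one exceeds 1.960 in absolute value is 8.8%, 8.3% or 7.7% for BSI shares of 1/3, 1/2 or 2/3, in place of 5%.

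**The case against.** Several counter-arguments have weight.

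- **A reader might infer that the trial has two primary endpoints.** It does not declare co-primaries. It has two competing definitions, and the explicit clash is between the synopsis and one sentence in 5.2. Section 5.6 A supports the wider reading without calling itself primary.
- **A reader might infer that the wider endpoint is underpowered.** The documents do not show this. Section 4 expects clinical sepsis to fall as well. If it is halved, the composite has more power than BSI alone; with a 25% fall, power is about what was planned.
- **The planned exposure may exceed the stated requirement.** Section 5.9 cites a census of 45,000 patient days a year. At 45,000 days per group, power for the composite with sepsis unaffected at 1 per 1000 would be 94%. That census covers the whole unit, however, and is not restricted to consented infants meeting the weight and age criteria. It is an upper bound.
- **A reader might infer that the plan inflates the type I error.** Nothing in the protocol plans a choice of endpoint after the data are known, and an analysis plan not shown here might fix the order. The 8% to 9% is the risk if the conflict stays open.
- **Bias.** Section 5.7 has infectious events evaluated by someone independent who does not know the bathing period. This reduces the bias concern but does not remove it, because staff who know the period order the cultures and antibiotics.

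None of this says which definition decides the trial. An analysis plan may specify methods, but the protocol's contradiction about its own primary endpoint remains.

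**Conclusion.** The concern holds as a contradiction within the protocol: the primary endpoint is BSI in the synopsis and BSI/CLABSI with culture-negative sepsis in 5.2. The sample size supports only the first, and the stated 80% power does not apply to the second.

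The size of the consequence cannot be fixed from the document. Under the assumed sepsis rates and effects, composite power runs from 41% to 99%. This rests on a BSI rate of 2.5 per 1000, a two-sided test, independent patient days and exactly 18,548 days per group. The direction depends on how far clinical sepsis responds, which the protocol does not quantify. The point should be settled before any data are seen, because the choice determines what counts as a positive trial.

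**What to change.** Name one primary endpoint and use it consistently in the synopsis, 5.2, 5.6 A and the first sentence of 5.9.

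- **Cheapest option:** culture-positive BSI per 1000 patient days, which matches the synopsis and the existing sizing. Clinical sepsis, and BSI plus clinical sepsis as a composite, become secondary outcomes. The Cox regression sentence in 5.9, which lists primary bloodstream infection, clinical sepsis and resistant-organism acquisition side by side, should be aligned with this order.
- **If the composite is to remain primary:** amend the synopsis, state the assumed rate of clinical sepsis and the expected effect on it, and restate the power for the composite.

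The first option costs wording changes and no extra data. Its downside is fewer events in the decisive analysis. The second needs a local estimate of the clinical sepsis rate and a new power calculation, which may call for more or fewer patient days than now stated.
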